## Abstract

**Background:**

Many emerging adults (EAs) are prone to making unhealthy choices, which increase their risk of premature cancer morbidity and mortality. In the era of social media, rigorous research on interventions to promote health behaviors for cancer risk reduction among EAs delivered over social media is limited. Cancer prevention information and recommendations may reach EAs more effectively over social media than in settings such as health care, schools, and workplaces, particularly for EAs residing in rural areas.

**Objective:**

This pragmatic randomized trial aims to evaluate a multirisk factor intervention using a social media campaign designed with community advisers aimed at decreasing cancer risk factors among EAs. The trial will target EAs from diverse backgrounds living in rural counties in the *Four Corners* states of Arizona, Colorado, New Mexico, and Utah.

**Methods:**

We will recruit a sample of EAs (n=1000) aged 18 to 26 years residing in rural counties (Rural-Urban Continuum Codes 4 to 9) in the Four Corners states from the Qualtrics’ research panel and enroll them in a randomized stepped-wedge, quasi-experimental design. The inclusion criteria include English proficiency and regular social media engagement. A social media intervention will promote guideline-related goals for increased physical activity, healthy eating, and human papillomavirus vaccination and reduced nicotine product use, alcohol intake, and solar UV radiation exposure. Campaign posts will cover digital and media literacy skills, responses to misinformation, communication with family and friends, and referral to community resources. The intervention will be delivered over 12 months in Facebook private groups and will be guided by advisory groups of community stakeholders and EAs and focus groups with EAs. The EAs will complete assessments at baseline and at 12, 26, 39, 52, and 104 weeks after randomization. Assessments will measure 6 cancer risk behaviors, theoretical mediators, and participants’ engagement with the social media campaign.

**Results:**

The trial is in its start-up phase. It is being led by a steering committee. Team members are working in 3 subcommittees to optimize community engagement, the social media intervention, and the measures to be used. The Stakeholder Organization Advisory Board and Emerging Adult Advisory Board were formed and provided initial input on the priority of cancer risk factors to target, social media use by EAs, and community resources available. A framework for the social media campaign with topics, format, and theoretical mediators has been created, along with protocols for campaign management.

**Conclusions:**

Social media can be used as a platform to counter misinformation and improve reliable health information to promote health behaviors that reduce cancer risks among EAs. Because of the popularity of web-based information sources among EAs, an innovative, multirisk factor intervention using a social media campaign has the potential to reduce their cancer risk behaviors.

**Trial Registration:**

ClinicalTrials.gov NCT05618158; https://classic.clinicaltrials.gov/ct2/show/NCT05618158

**International Registered Report Identifier (IRRID):**

PRR1-10.2196/50392

## Introduction

### Background

Emerging adulthood is an important habit-forming period of life. The lives of emerging adults aged 18 to 26 years are in flux [1], as they experience lifestyle transitions and increased autonomy while taking on adult-related responsibilities (eg, financial, residential, and employment). It is an important time for health behaviors because with increased autonomy, numerous emerging adults are at risk of making unhealthy choices [2,3].

Health-compromising behaviors that increase cancer risk later in life are especially prevalent among emerging adults [4] and are linked to future cancer morbidity and mortality [5]. Many emerging adults have reduced physical activity and unhealthy eating patterns that do not meet the 2020 American Cancer Society guidelines [6] (are overweight, eat fast food [7,8], and have low self-efficacy for making healthy food choices) [9-13]. Emerging adults’ use of nicotine products [9-12,14] and multiple combustible and noncombustible products [15,16] and their alcohol use and heavy drinking (bingeing) are high [17,18]. Emerging adults are also more prone to intentional UV exposure (solar and artificial tanning) [19]; sporadic sun safety practices [20-23]; and a lack of human papillomavirus (HPV) knowledge [24,25], resulting in incomplete vaccination rates [26,27]. These modifiable cancer risk behaviors are important targets of primary prevention for emerging adults by promoting moderate to vigorous physical activity (MVPA) and dietary and sun safety skills, supporting the use of brief interventions for tobacco or alcohol use, and encouraging emerging adults to make their own health care decisions such as HPV vaccination. However, there is a lack of rigorous research on interventions for emerging adults, and information on their cancer risk behaviors is limited [28].

In the United States, rural populations have substantially higher rates of cancer [29] related to unhealthy eating [30,31], high rates of smoking and alcohol use, exposure to UV radiation and radon (riskier for smokers) [32,33], and persistent HPV infection compared with urban populations. Rural cancer disparities are exacerbated by a lack of health insurance and preventive care [34,35], low socioeconomic status [36,37], poor health literacy [36,38], fatalistic beliefs and ambiguous health information [25], and pervasive barriers to preventive health care [37,39,40].

Social media may offer a superior intervention channel for reaching and influencing emerging adults compared with health care, schools, and workplaces, including in rural areas. Emerging adults (90%) are the most engaged age group on the internet [41], and the internet is a preferred channel for health information among rural and urban emerging adults [40,42]. Rural adults use the internet (85%), as do most Hispanic (86%) and African American (85%) individuals [42]. Social media platforms are very popular with emerging adults [41,43]. Social media provide flexible, responsive, accessible, and low-cost platforms for distributing cancer information to the public from trusted voices [44]. Social media can improve information dissemination, credibility, and relevance and are often used to detect and respond to emerging issues [45] and promote engagement with personalized and impactful user-generated content [46]. Although use varies across platforms, there is growing evidence that interventions delivered using social media can improve physical activity, diet, nicotine product use, skin cancer prevention, and HPV vaccination outcomes among young adults [47-57]. By contrast, it can be challenging to implement a cancer prevention intervention in health care organizations, schools, and workplaces in low-resourced rural communities. Interventions in these channels also may not reach many emerging adults who have low preventive health care use, school enrollment, or employment. However, social media platforms also circulate inaccurate, misleading, and harmful information [58,59]. For instance, social media has spread misinformation on tobacco products [60], breast cancer prevention [61], the efficacy of cannabidiol for cancer care [62], cancer-related nutrition [63], and the mistrust of HPV vaccines [64,65], which can undermine cancer prevention efforts. Thus, interventions also need strategies to correct misinformation and provide digital and media literacy skills [66-70].

In summary, emerging adulthood is an important period for establishing cancer prevention. Many rural emerging adults experience several cancer risk factors, but successful interventions for them are lacking. With the popularity of web-based resources for emerging adults, an innovative multirisk factor intervention over social media has the potential to reach this underserved population and reduce emerging adults’ cancer risks. The goal of this trial is to modify cancer risk factors among emerging adults aged 18 to 26 years living in rural counties in the Four Corners states of Arizona, Colorado, New Mexico, and Utah using a unique, theory-based social media campaign designed with community advisers that delivers relevant, credible, and timely content on reducing multiple cancer risks to emerging adults. A multirisk factor approach [71,72] is adopted because (1) emerging adults vary in cancer risk profiles, (2) several risks cooccur and are affected by similar mechanisms [73-76], and (3) coverage of a variety of topics in the campaign will be engaging. Furthermore, the Four Corners region has a relatively high burden of poverty [77,78], significant population diversity with large Hispanic and American Indian populations [79], and low population density where distance and transportation are health care access barriers [37,80], providing a rich environment to test the efficacy of a multibehavior health promotion intervention.

### Objectives

Our proposed intervention will aim to aid rural emerging adults in making informed decisions to reduce cancer risks related to infrequent physical activity, unhealthy diet, alcohol intake (per 2020 American Cancer Society guidelines [6]), nicotine product use, UV exposure, and lack of HPV vaccination uptake. In addition, it will help them critically evaluate and resist misinformation and marketing that promote cancer and other health risk behaviors and support emerging adults to be media literate when using digital media. The trial will test the following hypotheses:

Hypothesis 1: emerging adults will increase MVPA and healthy eating patterns, reduce nicotine product and alcohol use and sunburns, and increase HPV vaccine uptake from baseline to final assessment when receiving the social media intervention.Hypothesis 2: the positive impact of the social media campaign on cancer risk factors among emerging adults will be mediated by improved cancer risk knowledge and beliefs (ie, self-efficacy and response efficacy, norms, social support, and vaccine antecedents), digital and media literacy skills, misinformation identification, and family communication.

Analyses will also explore whether the impact of the campaign differs according to (1) the level of emerging adults’ engagement with it, (2) cancer risk factors, and (3) the biological sex of the participants. The prospective randomized quasi-experimental design and its large sample will provide a rigorous evaluation of the social media campaign compared with many previous studies on social media that have used less rigorous nonrandomized controlled trial designs and small samples [81-86].

## Methods

We will test a social media campaign to reduce cancer risk factors among emerging adults in rural counties in the Four Corners states using a randomized stepped-wedge trial design.

### Target Population and Recruitment Procedures

Emerging adults (N=1000) aged 18 to 26 years residing in rural counties in the states of Arizona, Colorado, New Mexico, and Utah will be enrolled in the study (refer to Textbox 1 for the inclusion and exclusion criteria). Many emerging adults will report ≥1 cancer risk behavior and will be residing in a variety of living arrangements, from multigenerational families to roommates to spouses or partners to alone. In the Four Corners states, 99 counties are rural (ie, Rural-Urban Continuum Codes [RUCC] 4 to 9 [87]), with >2 million residents (176,737 residents aged 19 to 25 years; annual income) [88]. Pregnant individuals will be excluded because the intervention will not provide individualized counseling and could lead to behavioral changes in diet or exercise that might be contraindicated during pregnancy.

Inclusion and exclusion criteria for the sample of emerging adults.
**Inclusion criteria**
Member of the Qualtrics survey panel in year 2Aged 18 to 26 yearsResides in a county coded as Rural-Urban Continuum Codes 4 to 9 in Arizona, Colorado, New Mexico, or UtahAble to speak and read EnglishHas regular social media engagementAccepts screening call from the study staffProvides consent to participate
**Exclusion criteria**
Participated in community engagement activitiesCannot speak and read EnglishHas low or no social media engagementDoes not accept a screening call from the study staffDoes not provide consent to participateDoes not give permission for engagement data to be extracted from the Facebook private groupsIf biologically female, currently pregnant

Emerging adults will be recruited from Qualtrics’ research panel, built from multiple providers that use by-invitation or double opt-in methods. Qualtrics will select adults aged 18 to 26 years residing in counties designated as RUCC 4 to 9 in the 4 selected states [87], balanced on gender, and refer emerging adults to the project’s registration website to complete a consent form. Fake, duplicate, and unqualified respondents will be screened out, and steps will be taken to ensure that they participate only once. The project staff will contact the consented emerging adults by telephone and confirm their eligibility. To avoid clustering, only 1 emerging adult per household will be enrolled. If recruitment lags, we will add Mountain West states with similar populations (ie, Idaho, Montana, Nevada, and Wyoming). We will use quotas so that the sample matches the education and the race and ethnicity of the counties. Although research panel members are required to have internet access, selection bias will be reduced as most US adults (90%), including emerging adults (100%) and rural adults (85%), have access to the internet [42]. We will confirm that the emerging adults have regular social media use (post ≥1 time per week) to allow them to engage with our campaign. We acknowledge that this criterion may impact generalizability, but social media influence those who view them regularly [89,90]. The escalating compensation schedule is designed to achieve retention for postintervention assessments.

### Randomized Stepped-Wedge Trial Design

The cancer prevention social media campaign will be tested using a randomized stepped-wedge design (Figure 1).

**Figure 1 figure1:**
[figure not shown]
Randomized stepped-wedge trial design.

Following baseline assessment (T_0_), emerging adults will be stratified by state, ethnicity (racial and ethnic minority individuals vs non-Hispanic White individuals), and biological sex (male vs female) and randomly assigned to 1 of 4 cohorts differing in intervention duration by the project biostatistician. All cohorts will complete postintervention assessments at weeks 13 (T_1_), 26 (T_2_), 39 (T_3_), 52 (T_4_), and 104 (T_5_). All data collection will be conducted using the secure web-based REDCap (Research Electronic Data Capture; Vanderbilt University) application. The primary outcomes measured at all assessment times will be MVPA, healthy eating patterns, nicotine product use, alcohol intake, sunburn, and HPV vaccination.

The social media campaign will be conducted over 12 months in 4 separate Facebook private groups. The intervention will start in each cohort at successive 13-week intervals, so cohorts will receive varying doses of campaign exposure (ie, 180 posts per 13-week interval) via stepped entry. Specifically, cohort 1 (250/1000, 25%) will start the social media campaign at week 1, receiving approximately 720 posts in 52 weeks. Cohort 2 (250/1000, 25%) will start the campaign at week 13 (approximately 540 posts), cohort 3 (250/1000, 25%) at week 26 (approximately 360 posts), and cohort 4 (250/1000, 25%) at week 39 (approximately 180 posts). Emerging adults will be told to read, react to, and comment on posts as often as they like. Exposure to cancer risk information and misinformation from other sources will be controlled by randomization.

The stepped-wedge quasi-experimental design was selected because it has several methodological advantages [91]. First, it allows for the random assignment of participants to 1 of the 4 cohorts, ensuring that potential confounding factors are evenly distributed across the groups. Each cohort is assigned to start the intervention at different times, creating a staggered, time-sequenced implementation schedule across the cohorts that creates the controlled nature of our trial. This design element allows for the within-study comparison of outcomes across different cohorts, with each cohort serving as a control for the others before they receive the intervention. Specifically, the control condition is represented by the periods when the cohorts have not yet started the intervention. For example, cohort 2 serves as a control group for cohort 1 before they commence their intervention in week 13. Second, the design also allows for comparisons between cohorts that have received the intervention for different durations. Third, by collecting data at multiple time points (T_1_-T_5_), the design facilitates the assessment of outcomes over an extended period that allows for the evaluation of trends and changes in outcomes over time within each cohort as well as comparisons between cohorts. The multiple baseline measures in cohorts 2, 3, and 4 will permit the examination of any trends or patterns before the intervention is introduced and will control threats to validity [92], as we can account for potential confounding factors, such as time-related effects or external factors, and compare cohorts at different stages of intervention exposure. This strengthens the internal validity of the study. Fourth, the design optimizes study resources by focusing on recruiting and retaining a longitudinal sample. This approach differs from securing a sample where half remain untreated, mitigating problems associated with control groups such as loss to follow-up, demoralization, disengagement, or noncomparability. It adheres to ethical standards by having all participants eventually receive the intervention but still preserves the controlled trial’s integrity.

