#### Implementation of Social Media Campaign

The social media campaign will be implemented through Facebook private groups. A staff person will serve as the community manager and schedule posts twice a day on all 7 days of the week (1 message in the morning and 1 in the afternoon) to achieve reach [142,143]. In each cohort, emerging adults will receive welcome posts on purpose and ground rules (eg, respect for others) and then receive the ongoing feed delivered in their separate private group so that posts are identical across cohorts, timely, linked to current events and news stories, relevant for seasons, and engaging. We will not start each cohort at the beginning of the feed because it would require adjusting earlier posts to be current, making them dissimilar across cohorts. The community manager will monitor reactions and comments from emerging adults, answer questions, address uncertainty, and correct misinformation [58,124,133]. The community manager will promote peer influence by, for example, (1) recruiting high-frequency emerging adult users to be guest moderators for up to 3 days to schedule posts and reply to comments and (2) hosting Facebook Live events with emerging adult experts (eg, an emerging adult dietitian). If any bullying arises, the community manager will de-escalate it by (1) highlighting empathy and (2) sending direct messages to stop it. If participants leave a group, they will be contacted to see why. Project staff, except the community manager and the project coordinator, will be blinded to the cohort membership.

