### Statistical Analysis Plan

#### Hypothesis Testing

We plan to use advanced statistical methods suitable for stepped-wedge designs to compare outcomes between different cohorts and time points, which will account for both time effects and intervention effects. This includes using mixed-effects models or generalized estimating equations that can adjust for time-related trends and cohort effects. In addition, by comparing cohorts that start the intervention at different times, we will isolate the effect of our campaign from other external factors and assess whether changes in the cancer risk behaviors are more pronounced or accelerated following the introduction of our intervention compared with the periods before the intervention. In addition, our analysis will adjust for potential confounding factors that might influence cancer risk behaviors, such as age, sex, ethnicity, and other relevant sociodemographic factors. This approach ensures that the control aspects of the design are rigorously analyzed.

Specifically, the 2 hypotheses and exploratory research questions will be tested using R (R Foundation for Statistical Computing) [179] and Mplus, V8.2 (Munthén & Munthén) [180], a structural equation modeling program that allows for growth models and latent constructs (to model measurement error appropriately), repeated measures, direct and indirect effects, and moderators using interaction terms and multiple group analysis [181]. Mplus will handle missing data via full information maximum likelihood. All tests will be intent to treat. To mitigate false discovery (type I error), an α of .008 will be used (ie, the traditional α=.05÷6 [number of cancer risk factors considered]) [182]. Once the full sample is recruited, baseline data will be described and plotted, measurement models will be assessed, and transformations for normality will be examined and applied.

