#### Power Analysis

To determine the appropriate sample size for the stepped-wedge design, we used the Shiny Cluster Randomized Trial calculator [188], setting α at .008 and assuming, conservatively, that the within-person correlation of the repeated measures is 0.5. Power analysis focused on the main effect on outcomes at the 104-week posttest score being significantly better than preintervention scores (ie, the time-averaged intervention effect). We considered a mean standardized difference between pre- and postexposure measure of 0.2 for a continuous outcome and a difference in pre- versus postexposure prevalence of 0.40 versus 0.48 for a binary outcome. These are conservative and relatively small effects based on our past assessment of a social media campaign [166,189] and the expectation that emerging adults are unlikely to see all posts. We will achieve a power of 0.80 with 115 people per cohort for a continuous outcome and 175 per cohort for a binary outcome. We have planned for a 30% (300/1000) dropout rate, so we will enroll 1000 emerging adult participants and expect to finish the trial with approximately 175 individuals in each cohort. We will use full information maximum likelihood methods for estimation; thus, even incomplete cases will be retained.

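### Each cohort is one interactive Facebook group, and the stated power and primary model make no allowance for correlation among its members; for a binary outcome a group ICC of about .002 is enough to lose the stated 0.80 power

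*Protocol article*

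**What the plan says.** Randomized Stepped-Wedge Trial Design assigns individuals at random to four cohorts of 250 and states: "The social media campaign will be conducted over 12 months in 4 separate Facebook private groups". Implementation of Social Media Campaign confirms that each cohort has its own group. It makes interaction part of the treatment: "The community manager will promote peer influence by", among other means, using participants as guest moderators for up to 3 days.

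Clustering is mentioned once, under Target Population and Recruitment Procedures, and only for households: "To avoid clustering, only 1 emerging adult per household will be enrolled".

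Power Analysis reports "we used the Shiny Cluster Randomized Trial calculator", "setting α at .008 and assuming, conservatively, that the within-person correlation of the repeated measures is 0.5". No between-participant correlation is given. The effects are "a mean standardized difference between pre- and postexposure measure of 0.2 for a continuous outcome" and a prevalence of 0.40 versus 0.48 for a binary outcome. The stated sizes are 115 and 175 per cohort for power 0.80, and about 175 per cohort are expected to finish.

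Hypothesis Testing says that mixed models or GEE can adjust for time trends and cohort effects, and "an α of .008 will be used" for each of six risk factors. The specific primary model regresses six measures per person on calendar-time and exposure-time dummies. It names no group or group-by-time term.

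**The concern.** Members of one group read the same comments, replies and guest-moderated threads, and the campaign's own theory section relies on peer spread and social comparison. Some correlation among members after exposure is therefore plausible. It would begin when the group opens, which is also when the cohort's treatment indicator turns on. A model that knows only about correlation within a person then counts a shared group-level deviation as precise evidence of a campaign effect.

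With about 175 people per group, even a very small intraclass correlation matters: the usual design effect, 1 + 174 × ICC, is already 1.87 at ICC .005. At stake are the per-outcome .008 threshold, which exists to protect six primary tests, and the claimed 0.80 power.

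**Working it through.** **Inputs from the article:** alpha .008 (.05/6 = .0083), taken as two-sided; within-person correlation 0.5; effects 0.2 SD and 0.40 versus 0.48; 115 or 175 per cohort; four cohorts with staggered starts.

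**Assumed:** the group ICC, which the article does not give; and a layout of five assessments (T0-T4) or six (adding T5, all cohorts counted as exposed). A single time-averaged effect is used, as in Power Analysis, not the exposure-time dummies.

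**Step 1. The plan's own figure, with independent persons.** Fit the stepped-wedge model with categorical periods by generalised least squares, each person being a cluster of one. The variance of the treatment coefficient for one person per cohort is V1 = 0.30 (five periods) or 0.28 (six). Then n = (2.652 + 0.842)² × V1/δ².
- Continuous, δ = 0.2: 12.21 × 0.30/0.04 = 92 per cohort; with six periods, 85.
- Binary, δ = 0.08/√0.2448 = 0.162: about 140, or 131 with six periods.

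The stated 115 and 175 are larger. They give power of about 0.90-0.92 and 0.89-0.92, so they do not reproduce at 0.80, but they err on the safe side. The dropout step does reproduce: 700/0.70 = 1000.

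**Step 2. Add a shared group effect after exposure.** For cohort c with exposure indicator e, the covariance of the cohort means is R/n + ICC × [(1−p) diag(e) + p ee′]. Here R is the within-person correlation matrix. The fraction p is the share of the group effect that persists across assessments (0, .5 or 1). The weights stay those of the person-only model. True type I error = 2Φ(−2.652 × naive SE/true SE). Power with the correct SE = Φ(δ/true SE − 2.652).

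Example: six periods, n = 175, ICC .005, p = 1. Naive SE = √(0.28/175) = .0400 and true SE = .0534. The ratio is .749, so type I error = 2Φ(−1.987) = .047. Binary power = Φ(0.162/.0534 − 2.652) = Φ(0.38) = .65.

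**Results at 175 per cohort** (ranges over five or six periods and over p):

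| Assumed ICC | True SE | True type I error | Binary power |
|---|---|---|---|
| 0 | .040-.041 | .008 | .89-.92 |
| .001 | .043-.045 | .014 | .83-.87 |
| .002 | .046-.048 | about .02 | .77-.81 |
| .005 | .053-.056 | about .05 | .60-.65 |
| .01 | .064-.067 | about .10 | .41-.45 |
| .02 | .081-.085 | about .20 | .23-.25 |

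A continuous outcome has more room. At 175 per cohort its power is .83-.86 at ICC .005 and .63-.68 at .01. At the stated 115 it is .70-.74 at ICC .005.

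**Step 3. Does adjusting for cohort effects help?** With fixed cohort effects added, type I error is .041-.057 at ICC .005 and .085-.119 at ICC .01. It hardly moves, because a fixed effect removes only differences that were there before the switch.

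**Step 4. Would an independent group-by-assessment random effect be enough?** If the true group effect persists (p = 1), type I error with that term included and its variance known is still .013-.016 at ICC .005 and .036-.041 at ICC .02.

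**The case against.** A reader might infer that the plan declares participants independent, that type I error is inflated whatever happens, and that power is overstated outright. The documents do not support that.

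- The article lists only the fixed part of the primary model and mentions cohort effects. A statistical analysis subcommittee is still to be formed (Project Initiation and Administration). Not naming a random term in a condensed article is not a claim of independence. This stands. Only the power assumption and the number of groups are fixed here.
- The error inflation depends on the target. If the campaign affects nobody, individual randomisation gives no reason for correlation confined to exposed periods. If one group does better because of its moderators and threads, that is a real effect of the campaign as delivered. This also stands: the inflation concerns inference beyond these four groups.
- The ICC is unknown. Identical posts, a single community manager, short guest-moderator spells and stratified randomisation all limit divergence between groups. At ICC .001 binary power remains .83-.87. Power is therefore not overstated at every plausible value.
- The failure of 115 and 175 to reproduce at 0.80 might look like support. It is a separate discrepancy in the conservative direction, and it is what supplies the slack at ICC .001.

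What the objection does not remove is the coincidence of group opening with the treatment switch, which cohort adjustment cannot undo.

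**Conclusion.** The concern holds in conditional form. Nothing in the stated power calculation or primary model allows for correlation within the four groups that starts at exposure. For claims about the campaign in general, at 175 per cohort, the stated 0.80 power for a binary outcome is lost at an ICC of about .002 or above. At ICC .005 each nominal .008 test runs near .05. For claims confined to the four delivered groups, this inflation does not apply.

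These sizes rest on assumed ICCs, a two-sided test, a constant effect and known variance components. Estimating a group variance from four groups would do worse. The direction is secure; the magnitude is not known from the article.

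**What to change.** 1. **Power Analysis:** state that power assumes no between-participant correlation within groups, and restate it over a group ICC range of 0 to .02.
2. **Hypothesis Testing:** for each primary outcome, add a sensitivity analysis with a post-exposure group effect that has both a persistent and an assessment-specific component. Use fixed assumed ICC values (for example .002, .005, .01), because four groups cannot estimate the variance reliably.
3. **Reporting:** state whether the target is the campaign in general or the four groups as delivered. Limit any outcome that is significant only when this correlation is ignored to a statement about the four groups.

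The cost is wording and a modest amount of extra analysis, with wider intervals and a lower stated power.

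Optional: split each cohort into several parallel private groups that receive the same scheduled posts, which makes group variance separable from cohort. With five independent groups per cohort, an ICC of .005 contributes .005/5 = .001 to the variance of a cohort mean, which is the .001 row of the table. This adds moderation work and changes group size.
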